### Blinding

As this is a RCT evaluation for three models of interprofessional practice between medical physicians and DCs, the study participants, study coordinators or treating clinicians are not blinded to the participant’s treatment allocation. The primary and most of the secondary outcome measures are self-administered questionnaires distributed by the study coordinators. Participants complete these questionnaires on their own in a consult room at the Baseline Visit 1 and at the Month 3 evaluation. The Timed Up and Go Test is completed at these visits by an examining clinician who has not provided care to the participant during the 12-week active care phase of the study. Other follow-up assessments are collected via CATI conducted by trained interviewers who do not provide study treatments and who are masked to participant outcomes assessment data from all other time points. Study clinicians remain blinded to participants’ outcome data for the entire study period. All analysts and study investigators are blinded to treatment group until data analysis is completed.

### Qualitative interviews

Participants complete an individual qualitative interview at the end of the 12-week active care phase following all other outcome measures [114]. A semi-structured interview schedule guides the interview process with follow-up probes used to elicit the participant’s unique experiences in the clinical trial. In most cases, the project manager (who does not have day-to-day contact with participants) completes the interview session to encourage participants to speak freely about their experience in the study. When the project manager is not available, a SC trained in the interview protocol conducts the interview. Participants are asked questions about their interest in the clinical trial; overall experience in the study; treatment expectations and effect of treatment allocation on those expectations; perceived changes in back pain and other health conditions during active care; potential impact of illnesses, injuries or other setbacks on LBP progress and quality of life; treatment likes and dislikes; relationship with medical doctor and/or doctor of chiropractic; and perceptions of the collaborative care process. Participants provide written consent at the time of the informed consent procedure and verbal permission to audio-record the qualitative interview at the start of the session. To assure confidentiality, interviews are conducted in a private consult room with the door closed, participants are not identified by name during the interview, and only the participant ID number marks the audio-recording and transcripts. In addition, we conduct exit interviews with interested medical physicians and DCs who provided care to study participants to determine their perceptions of the feasibility and sustainability of the study model. All interviews are transcribed verbatim by an independent transcription service, reviewed for completeness and accuracy by the project manager, and imported into a qualitative data analysis computer database (NVivo-9, QSR International Pty Ltd., Doncaster, VIC, Australia) for analysis.

### Data management

The DCC handles the data management procedures for this clinical trial using modifications of data handling procedures described elsewhere [62]. The STaRS is comprised of multiple sub-modules integrated into one comprehensive study management web application that includes CATIs for phone screens and follow-up data collection, participant eligibility checks, treatment allocation, participant tracking, a tickler system, report generation and scheduling. The ASP.NET web application elements were programmed in C# and Structured Query Language (SQL) using Microsoft Visual Studio 2005 (Microsoft, Redmond, WA, USA) and Microsoft SQL Server Management Studio (Microsoft). User-friendly data entry interfaces were programmed with appropriate participant flow restrictions, validation schemes and skip patterns. The STaRS interfaces with the Central Participant Database and uses a Project/Users Permissions System to control project personnel access to web modules. The DCC added the Doctors’ Communication module to facilitate the secure transfer of participant research records and to provide file posting updates with automated e-mail notification to the DC and MD/DO clinicians who collaborate on LBP care for participants in the Shared Care group, as well as to the GFMC research nurse and PCCR project manager and senior clinician.

Participant self-report questionnaires and clinician-completed progress notes are paper-based forms. Research outcomes data collection paper forms include only the unique numerical participant ID as an identifier. Study coordinators provide oversight of all paper data collection forms, log each completed form into the form tracking module of STaRS, and submit data forms for key-entry. The project manager transfers paper records from the medical clinic to the DCC on a weekly basis. Forms are also transferred between clinics on secure fax systems. Paper data collection forms and participant research record charts are stored in locked filing cabinets at each clinic. Trained data-entry clerks double key-enter paper forms in a Microsoft Windows® (Microsoft) program using range and validation checks.

The STaRS web system is password-protected and uses a Microsoft® SQL Server (Microsoft) database platform to store all data. Web programmers collaborated with project personnel to gather system requirements and designed the web applications and database structures based on PCCR standards. DCC personnel developed the electronic data collection forms, programmed web applications to support data and project management, provide data form key-entry and technical support, and execute procedures for data security and data quality control, storage and back-up. The Data Manager maintains the data dictionaries and creates the datasets for analysis.

Participant enrollment data are collected at each stage of the clinical trial from initial phone screen through treatment allocation to the 12-week primary endpoint and 52-week follow-up period, so participant flow is reported according to CONSORT guidelines [62]. Specifically, we collect recruitment source, total responses per recruitment source, race/ethnicity and gender distribution, disposition status (for example, ineligible, does not wish to participate, allocated, withdrawal, completed active care, completed follow-up, lost to follow-up), reasons for non-participation or exclusion (for example, current treatment, cost, treatment allocation, perceived benefit, travel, health concerns, baseline exam results, multiple/other and so on), and the number allocated to each treatment group [66].

Data management and quality control of both key-entered forms and web forms are performed using SQL views, stored procedures and real-time, web-based reports. Automated reports are viewed by the data manager and project manager to determine if quality improvement actions must occur, such as improved documentation, protocol revisions or personnel retraining. Final project datasets of combined web and paper data are assembled by transferring data from Microsoft® SQL Server (Microsoft) to SAS System for Windows (Release 9.2, SAS Institute Inc., Cary, NC, USA). The data manager writes and tests SAS programs to create datasets as requested by the investigators and creates the data dictionaries. DBMS Copy (Conceptual Software, Houston, TX, USA) software is used to move the data across software applications.

### Data and safety monitoring

A Data and Safety Monitoring Committee (DSMC) provides scientific and ethical oversight on all ongoing human clinical trials conducted by the PCCR. The DSMC currently is composed of epidemiologists with expertise in LBP and/or CAM clinical trials, a medical physician, a doctor of chiropractic and a biostatistician, none of whom are employed by PCCR or GFMC. The DSMC approved the study protocol, informed consent document and human research participant protection procedures before trial implementation. To monitor trial data, the DSMC reviews status reports prepared by the trial biostatistician that include recruitment accrual, enrolled participant baseline characteristics and other enrollment data; data collection form processing; follow-up assessment completion; treatment compliance; study protocol deviations and other clinical trial data. To monitor participant safety, the DSMC reviews reportable adverse events (see below) every six months and assesses any serious adverse events upon report receipt. No formal stopping rules were established in advance of trial implementation. The DSMC may make recommendations to the principal investigator and funding agency regarding study progress, termination or trial modifications. We also report serious adverse events to the funding agency following receipt of the report.

### Adverse events and UPIRTSOs

An IRB-approved adverse event (AE) grading and reporting protocol defines the processes by which AEs are monitored and categorized in this clinical trial. This protocol also outlines when and how participant safety concerns are reported to the IRBs, DSMC and funding agency. An AE is defined as any untoward medical occurrence that may present itself during the conduct of the study and that may or may not have a causal relationship with study procedures [115]. A serious adverse event is defined as an adverse event resulting in any of these outcomes: death, a life-threatening adverse experience, hospitalization or significant disability/incapacity [115]. A previous clinical trial of six weeks of chiropractic care or medical care for persons over age 55 years with LBP reported no serious adverse events associated with any of the interventions and only 21 side effects in 20 participants among 240 randomized participants [27].

Our research center uses an active process of clinical surveillance [116] to monitor adverse events and other changes in participant health status throughout the course of our studies. Research clinicians, SCs and the GFMC research nurse receive ongoing training on AE identification, grading, reporting and monitoring. Participants also are instructed to report new symptoms or changes in health status to the research team at each treatment visit and to contact the clinics in the event of pain, discomfort or other clinical concerns they believe may be related to study treatments. Research clinicians monitor participant safety by conducting clinical evaluations of health status and querying participants for new symptoms or other changes in health status, alterations in prescribed or self-care treatments, and the development of any untoward effects from study interventions at each treatment visit and all follow-up assessments.

When AEs are suspected, the treating DC at the PRC or the research nurse at GFMC completes an AE monitoring form which includes a description of the event, date of onset, impact of prognosis and referral to outside care. The clinician or nurse then rates whether an AE is: 1) mild, moderate, severe or serious in severity; 2) expected (disclosed in the informed consent document or part of an underlying disease) or unexpected (more serious than expected, or not disclosed in informed consent document); and 3) related to the intervention (for example, definitely, probably, possibly, unlikely or unrelated). AEs are followed to resolution at which time an AE resolution form is completed. An automated web-based system records all AEs to allow the project manager and senior clinician to track and report adverse events to the principal investigator, both IRBs of record, DSMC and funding agency.

We also monitor and report Unanticipated Problems Involving Risks to Subjects or Others (UPIRTSOs). Federal regulations (45CFR46.103(b)(5) and 21CFR56.108(b)(1)) require study investigators to promptly report UPIRTSOs to local IRBs. The Palmer College of Chiropractic IRB defines UPIRTSO as any problem or event that in the opinion of the local investigator was unanticipated, serious and at least possibly related to the research procedures.

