### Medical care

All study participants receive conventional medical care from a family medicine resident who is supervised by on-site family medicine physician faculty at the GFMC. Medical care provided in this study includes standard therapies for back pain that occur over a 12-week time period. None of the medical treatments in this study are experimental. GFMC physicians follow the Joint Clinical Practice Guideline from the American College of Physicians and the American Pain Society [51]. The key principles of these recommendations include: a focused history and physical examination; limited diagnostic imaging restricted to select patients (that is, radiculopathy); education about self-management, including maintaining activity levels as tolerated, local heat or cold application, and exercises; pharmacologic management with the use of analgesics and anti-inflammatory agents; and additional therapies that may be applied for participants not responding to the initial interventions, including physical therapy and referral to a pain clinic. All medical care visits are staffed by attending physicians in addition to the resident physicians who are assigned to study participants.

Participants, their insurance company or Medicare are charged for the medical care delivered during the 12 weeks of active care. The minimum dose of conventional medical care for this study is one treatment visit to the family practice doctor. Medical care treatment visits last approximately 15 minutes, with additional visits scheduled as needed. Participants allocated to the Dual Care and Med Care groups receive medical care from a different subset of GFMC physicians than do the participants allocated to collaborative care treatments provided by Shared Care doctors (described below).

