
Participants are not charged for the chiropractic care delivered in this study, but may be required to pay on their own or to individually submit bills to Medicare or their insurance companies for co-interventions such as orthotics, monitored exercise programs or special equipment recommended by the DC. The minimum dose of chiropractic care is one treatment visit to the doctor of chiropractic. The typical chiropractic treatment visit is 15 to 30 minutes in duration, with the DC making recommendations regarding treatment frequency (for example, one, two or three times per week) and duration (for example, number of weeks) as the participant progresses through the 12-week active care phase.

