### Outcome measures

Outcomes are measured by participant self-report, objective assessment, and in-person and telephone interviews. Outcomes are collected at baseline, 4, 8 and 12 weeks (primary endpoint), and every 12 weeks thereafter for up to one year (weeks 24, 36 and 52). The baseline visits and 12-week evaluations are scheduled as in-person visits at each clinic. At these visits, a SC administers the self-report questionnaires and interviews to the participant and cleans the data per protocol. Study clinicians (MD/DO and DC) perform the objective clinical assessments. DC exams are conducted by examining clinicians who do not treat participants as part of this trial; GFMC treating physicians complete the 12-week MD/DO exams with their assigned participant to maintain continuity of care. Due to logistical constraints with the doctors’ schedules, pre- and post-evaluations may not necessarily be completed by the same clinicians. A semi-structured qualitative interview is conducted by the project manager or SC at the PRC during the 12-week evaluation after completion of all other assessments to understand the participant’s perceptions of back pain improvement, clinical trial experience, expectations, treatment effects and interprofessional collaboration among the treating clinicians. We attempt to obtain outcome data from all trial participants, even those who decide to not attend treatment visits, drop out of care or move away from the area. If a participant is unable to attend the 12-week visit in person, the primary outcome measures and a subset of secondary outcomes are administered via CATI or paper-based questionnaires sent to the participant’s home with a stamped return envelope.

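### Adverse events are queried at every treatment visit, so counts may look higher in the two chiropractic arms at equal true risk; separately, seriousness is graded as a level of severity

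*Protocol article*

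**What the plan says.** Under Adverse events and UPIRTSOs, research clinicians are to ask about new symptoms, changes in treatment and "the development of any untoward effects from study interventions at each treatment visit and all follow-up assessments". Participants are also told "to contact the clinics in the event of pain, discomfort or other clinical concerns they believe may be related to study treatments". The Study treatments section repeats that providers ask at each treatment visit.

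The number of treatment visits depends on arm. For medical care, which every arm receives, "The minimum dose of conventional medical care for this study is one treatment visit to the family practice doctor", "with additional visits scheduled as needed". Dual Care and Shared Care add up to 12 weeks of chiropractic care. Here too "The minimum dose of chiropractic care is one treatment visit to the doctor of chiropractic", and the example frequencies are one, two or three visits a week. Chiropractic visits are free to the participant, while medical visits are billed. The assessment schedule does not depend on arm: "Outcomes are collected at baseline, 4, 8 and 12 weeks (primary endpoint), and every 12 weeks thereafter".

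The treating chiropractor at the research clinic, or the research nurse at the family medicine clinic, completes the adverse event form. That person rates the event as "mild, moderate, severe or serious in severity", then rates expectedness and relatedness. The same section defines a serious event by outcome: death, a life-threatening experience, hospitalization, or significant disability or incapacity.

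**The concern.** There are two separate problems.

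**Ascertainment depends on arm.** Chiropractic visits come on top of the medical care that all arms get, and each one carries an active query. A minor or short-lived event is then more likely to be asked about while it is still remembered. Safety is a monitored outcome, and the Background names safe combination of the two kinds of care as a gap in the evidence. Counts by arm will therefore be compared even without a formal test. The person completing the form also differs by clinic, and Med Care participants have no chiropractic treatment visits.

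**Two attributes share one scale.** Severity is intensity; seriousness, as the article defines it, is an outcome. An event of moderate intensity that leads to hospitalization fits two of the four levels. Graded as serious, its intensity is not in the grade. Graded as moderate, its seriousness is not. The second matters more: under Data and safety monitoring, serious events go to the monitoring committee on receipt and to the funder, and seriousness is part of the definition of a reportable unanticipated problem.

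**Working it through.** The article gives no adverse event rate, visit total or between-arm comparison for this trial, so there is no figure to reproduce.

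**Step 1. Query points in the 12 weeks of active care.** Add medical visits, chiropractic visits and the three common assessments (weeks 4, 8 and 12).

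- Med Care at the minimum: 1 + 3 = 4. With three medical visits: 3 + 3 = 6.
- Dual or Shared Care at the minimum: 1 + 1 + 3 = 5.
- Dual or Shared Care with chiropractic care kept up for 12 weeks: weekly, 1 + 12 + 3 = 16; twice weekly, 1 + 24 + 3 = 28; three times weekly, 1 + 36 + 3 = 40.

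**Step 2. From query points to recorded events, with equal true risk.** Assumptions, none of them in the article:

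- Onset is uniform over 84 days, and the single medical visit falls early.
- An event is recorded if it is captured at any later contact up to week 12.
- The chance of capture at a contact is p0 × 0.5^(lag/half-life), independent across contacts.

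As a hand check, consider only the next contact after onset. Mean capture over a gap of L days is p0 × (h/ln 2)/L × (1 − 0.5^(L/h)). With p0 = 0.9 and h = 7 days:

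- L = 28: 0.9 × (10.10/28) × 0.9375 = 0.30
- L = 7: 0.9 × (10.10/7) × 0.5 = 0.65

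The ratio is about 2.1. Allowing capture at later contacts and at the medical visit gives 0.34 against 0.86, a ratio of 2.5.

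Simulated share of events recorded, p0 = 0.9, one medical visit in each arm, chiropractic care for 12 weeks (ratio to Med Care in brackets, from unrounded values):

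| Recall half-life | Med Care | Chiropractic 1 per week | Chiropractic 3 per week |
|---|---|---|---|
| 3 days | 0.16 | 0.57 (3.5) | 0.91 (5.6) |
| 7 days | 0.34 | 0.86 (2.5) | 0.99 (2.9) |
| 14 days | 0.55 | 0.96 (1.8) | 1.00 (1.8) |
| 28 days | 0.74 | 0.99 (1.3) | 1.00 (1.3) |
| no decay | 0.96 | 0.99 (1.03) | 1.00 (1.04) |

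**Step 3. Sensitivity.**

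- p0 = 1.0 and no decay: ratio 1.00.
- Minimum visits in both: 1.01 to 1.10.
- Three medical visits in Med Care against one medical visit plus 12 weeks of chiropractic care, p0 = 0.9: about 1.8 to 2.1 at 7 days and 1.4 at 14 days.
- The same, but with chiropractic care weekly for only six weeks: 1.5, 1.2, 1.05 and 0.98 at half-lives of 3, 7, 14 and 28 days.
- p0 = 0.5, half-life 3 days, three chiropractic visits a week: 7.5.

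**Step 4. Common assessments only.** Query points are 3 against 3, so the expected ratio at equal risk is 1.0 by construction. This requires that everyone is asked the same question and that an event counts there even if a treatment visit has already recorded it.

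**Step 5. The grading scale.** No arithmetic applies. The outcome-based definition and the four-level severity rating stand in the same section and cannot both describe one single-choice item.

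**The case against.** The strongest reply is that the arms are not as different as they look. The weeks 4, 8 and 12 queries and the spontaneous route are open to every arm, the stated minimum is one visit for each kind of care, and medical visits continue as needed. The article gives frequencies only as examples and no totals. It plans no between-arm test of adverse events, and safety tables are commonly left to an analysis plan. Asking at each visit also protects participants. All of this stands. It limits the size of the point and makes it one about descriptive counts, but it does not remove the arm-dependent schedule.

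A reader might infer that counts in the chiropractic arms will be several times higher, for example by giving each visit a fresh 5 to 10% chance of a recorded event. The article does not support that. It gives no such probability, and the calculation lets true risk grow with the number of questions. The common assessments must also be counted. Even in that formula, 5 against 17 queries gives 1 − 0.95^5 = 23% against 1 − 0.95^17 = 58%, or 41% against 83% at 10%: ratios of 2.6 and 2.0.

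On grading, an IRB-approved grading and reporting protocol exists but is not shown, and it may hold two fields. So it cannot be said that intensity is lost for every serious event. The form also carries a description, from which either attribute might be recovered. The article's wording still conflicts.

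**Conclusion.** Both parts hold in limited form.

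The plan gives Dual and Shared Care more occasions than Med Care to record an event, so their counts may, not will, look higher at equal risk. The ratio runs from 1.0 (full capture) and 1.01 to 1.10 (minimum visits) to about 1.3 to 5.6 (weekly or more frequent visits for 12 weeks, half-life 28 to 3 days, p0 = 0.9). With short chiropractic courses and several medical visits it can vanish. Recall, capture and visit numbers are all assumed, so the direction is plausible but the size is not established. For scale, the earlier trial that the article cites had side effects in 20/240 = 8.3% of participants. If Med Care recorded that share, it would be about 3 of 40, and a ratio of 2 would make it about 7 of 40. The contrast affected is Med Care against the two chiropractic arms; the article gives no reason for visit numbers to differ between Dual and Shared Care.

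The severity and seriousness conflict needs no assumption. The definition and the rating scale must be reconciled.

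**What to change.** 1. Code severity (mild, moderate, severe) and seriousness (yes or no, by the article's outcome definition) as two items.
2. Where the source can be recovered, classify each event as reported at a common scheduled assessment, at a treatment visit, or spontaneously. Show the first group in its own table by arm and the other two separately, with the number of contacts per arm beside the counts.
3. Keep all serious events in one table, whatever their source.
4. Carry the source flag and the two-item grading into the full-scale trial, and state who asks the question at the telephone follow-ups. The article assigns the query to research clinicians, but interviewers who do not treat participants make those calls.

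The cost is coding and a few table shells. Active care ended in November 2012, so coding for this pilot is retrospective and the source may not always be recoverable. The arm-comparable table will hold fewer events, and short-lived treatment reactions may appear only in the visit-elicited table, so neither table should be read alone.
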